## Discussion

The aim of this paper is to describe a N-RCT regarding a recovery workshop being implemented in community mental health services in Catalonia, Spain.

The WRAP [27], a similar tool created in the USA, has been widely implemented and evaluated, and is currently recognized as an evidence-based intervention by the Substance Abuse and Mental Health Service Administration [43]. In contrast, there is little evidence regarding the efficacy of this type of interventions in non-English-speaking contexts and no study has been found in southern European or Spanish-speaking countries [25].

This study will provide data on the effectiveness of the recovery workshop of the *Activa’t per la Salut Mental* programme. Moreover, this effectiveness will be measured with psychometric instruments that assess variables of the CHIME model [11], with a perspective of recovery-oriented care. This differentiates it from the majority of previous studies, whose most evaluated variables are symptom improvement and knowledge, and attitudes towards recovery [25]. Furthermore, the psychometric instruments used in this study to assess personal recovery [33, 35] and empowerment [38] have been created by or with the participation of users and survivors as part of the research team. In this respect, these instruments share the philosophy of the paradigm shift. This is a perspective that recognizes users of mental health services as subjects of knowledge (i.e., experts by experience) and not as objects of an intervention.

In addition, this study will be the first to provide data of the effectiveness of a group recovery workshop designed to promote self-determination in the recovery process, in a Mediterranean cultural context, with a Latin language, a Catholic tradition and a characteristic family and cultural environment.

Finally, a workshop intended to promote personal recovery is implemented for the first time in the community rehabilitation services in Catalonia. This evaluation is conducted in order to assess the possible inclusion of the workshop into the portfolio of mental health services in our country, as has happened with other previous projects of the *Activa’t per la Salut Mental* programme.

The study protocol has two limitations that should be pointed out. Firstly, we have chosen a non-randomized trial design to do the study. Therefore, outcome evaluation could not be double-blinded. The main reason is that we wanted to include small cities in the sample as well. These populations have a smaller CRS, with fewer places offered and few users. Taking into account the fact that participation in the activities of the CRS is voluntary, there might be not enough people interested in participating in a 12-week training workshop to create a randomized control group. A pre-recruitment consultation revealed that this was the case for at least 3 CRS. Therefore, there is an evident bias, as the people in the experimental group are those interested in participating in a workshop aimed at promoting personal recovery, and the people in the control group are those not interested in this activity.

Secondly, the loss of subjects over the course of the 12-week implementation of the recovery workshop may cause a possible decrease in the statistical power and a selection bias. As this is a training workshop, offered as a voluntary activity, being implemented for the first time at the CRS, of which people had no prior references with respect to what it would be like to participate, it is expected that there will be a higher rate of abandonment of the activity than the average for the usual activities of the CRS. We expect an abandonment rate of around 20-25%. The possible bias risk here is that the people who complete the workshop and the evaluation are those who are most interested in or identify more with what the training offers them.

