### Sample size

A power analysis was conducted to determine the appropriate sample size. To do so, we used the G*Power software (Version 3.1.9.7) [32]. To detect differences in each group with repeated measures within-between factors (ANOVA) that correspond to a small effect size (0.18), with an alpha risk of 0.05, and a power of 80%, the adequate sample size required for this study in each group will be 64 participants. Assuming an attrition rate of 25% over the course of the three and a half months of the study, we estimate that a total sample of 160 users of a CRS will be required.

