### Statistical analysis

To evaluate the effectiveness of the *Activa’t per la Salut Mental* recovery workshop, descriptive statistics for characterizing the sample size will be performed. Multivariate analyses for repeated measure designs will be used for measures of personal recovery, empowerment, hope and perceived social support. Between-group and within-subject comparisons will be performed. In addition, ANOVA and ANCOVA will be used when comparing groups.

Statistical analyses will be performed using JASP software (Version 0.16.3) [42].

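### The protocol predicts heavier, possibly selective loss from the workshop group, but its named pre-post methods use only people with both measurements and its only provision is a larger sample

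*Protocol article*

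**What the plan says.** Four parts of the protocol article bear on this point.

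- **Discussion, second limitation.** On the size of the loss: "We expect an abandonment rate of around 20-25" per cent. On the comparison with usual care: "it is expected that there will be a higher rate of abandonment of the activity than the average for the usual activities of the CRS". The paragraph is framed as loss of subjects during the 12 weeks, which "may cause a possible decrease in the statistical power and a selection bias". It ends: "The possible bias risk here is that the people who complete the workshop and the evaluation are those who are most interested in" the training or identify most with it.
- **Sample size.** The calculation is for a within-between repeated-measures ANOVA with 64 per group. Loss is handled by enlarging the sample: "Assuming an attrition rate of 25% over the course of the three and a half months of the study", the total becomes 160.
- **Statistical analysis.** "Multivariate analyses for repeated measure designs will be used for measures of personal recovery, empowerment, hope and perceived social support". Then: "In addition, ANOVA and ANCOVA will be used when comparing groups". No analysis set is given.
- **Outcomes and participant timeline.** There is one measurement before and one after. The second is timed to about a week after the workshop ends at each service, not to the individual's attendance. The text does not say whether people who have left the workshop are asked for it.

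**The concern.** The protocol forecasts three things together: substantial loss, more of it from the workshop than from usual activities, and a possible link between staying and interest in the training. That is the pattern under which a complete-pairs comparison can be biased. With two time points, a classical repeated-measures ANOVA or multivariate test needs both scores, and so does an ANCOVA of the post score on baseline. Anyone without a post score leaves the comparison.

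Enlarging the sample protects power. It does nothing about selection.

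The text also lets two events run together: leaving the workshop and leaving the study. A person can do the first without the second, and the bias depends on the second.

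The result is meant to inform whether the workshop enters the public service portfolio (Discussion). That decision concerns users who are offered the workshop, of whom up to a quarter may not finish. An estimate from stayers alone could be too favourable. It would add to the self-selection into groups that the first limitation already concedes.

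**Working it through.** **The plan's own attrition figure.** 64 × 2 = 128, and 128 × 1.25 = 160, which is the stated total. Taking 25% off 160 leaves 160 × 0.75 = 120 pairs, and 20% off leaves 128. Dividing by the retained fraction gives 128 / 0.75 = 171. That shortfall is a separate matter. What counts here is that the allowance equals the top of the abandonment range and treats those people as supplying no usable pair.

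**General formula.** Let d be the fraction of a group without a post score, and δ the mean change of those retained minus the mean change of those lost. The mean change in all enrolled is (1 − d) × retained mean + d × lost mean. So the retained mean exceeds the mean in all enrolled by d × δ. For the difference between groups:

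bias = d_W × δ_W − d_C × δ_C (W = workshop, C = control).

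**Inputs.** d_W = 0.20-0.25 comes from the Discussion. That d_C is lower is suggested there, but no figure is given, so 0.10 is an assumption. All values of δ are assumptions.

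**Case A: the workshop works for stayers, leavers gain nothing and give no post score, and control loss is unrelated to change (δ_C = 0).**
- Ratio of the complete-pairs effect to the effect in all enrolled = 1 / (1 − d_W).
- At 25%: 1 / 0.75 = 1.33. For example, 0.50 SD is reported where all enrolled gain 0.50 × 0.75 = 0.375 SD.
- At 20%: 1 / 0.80 = 1.25.
- This is a deliberately unfavourable case. Someone who attends part of 12 sessions may gain something.

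**Case B: no true effect, the same δ in both groups, loss 25% against 10%.**
- Bias = (0.25 − 0.10) × δ = 0.15 × δ.
- δ = 0.5 SD gives 0.075 (0.08 rounded); δ = 1.0 SD gives 0.15.
- At 20% loss in the workshop group: (0.20 − 0.10) × δ = 0.05 to 0.10.

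**Case C: a check by another route.** Suppose the lowest fraction d on a normally distributed retention tendency is lost, and this tendency correlates r with the change score. The retained mean shifts by r × φ(z_d) / (1 − d), which is 0.35r at 20% loss and 0.42r at 25%. This is the shift in the workshop group alone, before any offset from controls.

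| r (assumed) | Shift at 25% loss, change-score SD |
|---|---|
| 0 | 0 |
| 0.1 | 0.04 |
| 0.3 | 0.13 |
| 0.5 | 0.21 |

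**When the bias vanishes.** If δ = 0 in both groups (equivalently r = 0), the bias is zero. If d and δ are equal in both groups, the two terms cancel. If leavers change more than stayers, the sign reverses.

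**The case against.** A reader might infer that the protocol analyses only workshop completers and so builds the bias in. The documents do not support that. No sentence restricts the analysis to completers or says that leavers are not measured. The post measurement is tied to the end of the workshop at each service, so a leaver who answers it has both scores and stays in a pre-post ANOVA. The motivated-completer pattern is stated as a possible risk and openly disclosed, not asserted as fact.

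Four further objections have force.

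- Analysis sets and missing-data methods are commonly left to a full protocol or analysis plan that is not shown. Their absence from an article is not itself a fault.
- The sizes above rest on assumptions. The Sample size section applies a single 25% rate to the whole sample and gives no lower figure for controls.
- Measuring leavers may take more effort than it seems. The battery has 1 + 4 + 12 + 40 + 12 + 12 = 81 items. The article names a digital platform but does not say that the questionnaire can be answered away from the service.
- A mixed model or imputation from baseline scores and sociodemographics corrects only the dropout that those variables explain. The driver that the protocol fears, interest in the training, is not among the variables listed.

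These points limit the wording and the size, but they do not remove the point. The article itself predicts loss that is unequal and possibly selective, describes abandonment as loss of subjects, and sizes the sample as if those people supply no pair. It then names methods that leave such a bias untouched. Disclosing a limitation does not replace a remedy that is at hand.

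**Conclusion.** The point holds in conditional form. The protocol predicts heavier loss from the workshop, warns that it may be selective, and commits to methods that use complete pairs, with a larger sample as the only provision. If leavers are not measured and retention is related to change, the workshop effect may be overstated.

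The illustrative size is an overstatement of up to a third, if 25% leave, gain nothing and give no post score. Alternatively, it is a spurious 0.08-0.15 SD with no true effect, given an assumed 10% control loss and an assumed gap of 0.5-1.0 SD. The bias can also be zero, as shown in the working. The documents do not establish that it will occur, nor that completers are in fact the most motivated.

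This should be corrected, because the remedy is cheap and the result feeds a service decision.

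**What to change.** 1. State that everyone enrolled is asked for the post questionnaire at the planned time, whether or not they finished the workshop, and is analysed in the group in which they enrolled. This step acts most directly on the bias.
2. For post scores still missing, use a likelihood-based mixed model or multiple imputation with baseline scores and sociodemographic variables. Say that this corrects only dropout explained by those variables.
3. Add a shift (delta) sensitivity analysis in which missing workshop outcomes are made progressively worse, and report how far they must move before the conclusion changes.
4. Report workshop completers as a secondary analysis, and give the numbers leaving the workshop and the numbers missing the post score separately, by group.

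Recruitment is described as having run to October 2022, so data collection may be over. In that case apply steps 2 to 4, keep in the analysis every leaver who did give a post score, and limit the conclusion to what the observed data support.

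The cost is some follow-up contacts by service staff, modest analysis work, and an estimate that may be smaller than the one for completers.

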## Data Availability

The dataset generated and analysed in this study will be available from the corresponding author. Results generated in this study will be published in peer-reviewed journals and presented at national/international conferences. The materials used in the recovery workshop are publicly accessible at https://activatperlasalutmental.org/lactivat/el-circuit-activat/psicoeducacio/#recuperacio: (1) Manual for Recovery and Self-Management of Well-Being; (2) Personal Workbook; (3) Guide to Implementing the Workshops.

## Abbreviations

N-RCT: Non-Randomized Controlled Trial
CRS: Community Rehabilitation Service
SISR: Self-Identified Stage of Recovery
MARS12: Maryland Assessment of Recovery in Serious Mental Illness Scale – Short
NEL: Netherlands Empowerment List
DHS: Dispositional Hope Scale
MSPSS: Multidimensional Scale of Perceived Social Support
